#### Mechanisms

We propose that the deliberative loop intervention will change stakeholder’ opinions and their perceptions of voice. To measure change in stakeholders’ opinions, we will quantify the absolute change in stakeholders’ rankings of their top five strategies (out of a total of eight possible) made at the beginning and end of the deliberative forum. For options that are not ranked at either the beginning or end of the forum, we will assign them a value of 6. Thus, for example, if an option was not ranked at the beginning of the forum but then ranked 3 at the end of the forum, we will calculate the change as 3.

We will measure stakeholders’ perceptions of voice, which we define as having the opportunity to share one’s views, in three ways. First, voice will be measured using the Promotive and Prohibitive Voice scales [21]. Both Promotive Voice and Prohibitive Voice will be assessed immediately following the deliberative forum, via the post-session survey. Stakeholders will complete the scales first as they characterize the deliberative forum and second as they characterize past UBT meetings. Each scale has five items and is scored on a 5-point Likert-type scale ranging from “Strongly Disagree” to “Strongly Agree.” Six-week test-retest reliability has been shown to be 0.42 for Promotive Voice and 0.44 for Prohibitive Voice. In validation studies, these scales have been shown to have convergent and discriminant validity. Confirmatory analysis that also included measures of psychological safety, felt obligation for constructive change, and organization-based self-esteem demonstrated that a five-factor model in which each scale loaded on a separate factor fit best.

Second, the post-session survey will also include questions addressing the stakeholders’ perceptions of leadership responsiveness to feedback in the past year (three questions) and anticipated responsiveness to the feedback from the forum. These questions are scored on a 5-point Likert-type scale ranging from “Strongly Disagree” to “Strongly Agree” and are followed by a free response box for comments and suggestions.

Third, we will review the transcripts from the deliberative forums using six codes to assess stakeholder voice. An example of one of the codes is as follows: “Suggest new behaviors which are beneficial to my clinic.”

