### Power

Power was calculated using the “stepped wedge” package in Stata 16 [15], based on the approach developed by Hussey and Hughes [16]. Our null hypothesis is that providers’ rates of placing or treatment planning sealants for occlusal NCCLs will not differ between the non-intervention and intervention periods. Our alternative hypothesis is that providers’ rates of placing or treatment planning sealants for occlusal NCCLs will increase following the intervention. We assumed a Type I error of 0.05 and a 3% rate of placing or treatment planning sealants in the non-intervention period and a 10% rate in the intervention period, which is an increase that is similar to that seen in similar interventions [17]. Scenarios were calculated using intraclass correlations of 0.01, 0.1, and 0.25 and *n*=50 as the average number of providers per clinic in a conservative scenario and *n*=60 in a more realistic scenario using provider counts from participating clinics. Randomizing 15 clinics along with 1 vanguard clinic using a stepped-wedge approach with these assumptions and under these scenarios, we will have at least 80% power and close to 100%.

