### Measures

Table 3 outlines the measures, sources, and timing for each construct in the conceptual model and study.

**Table 3 Tab3:** Theoretical constructs, measures, data sources, and timing of data collection

Theoretical construct	Measure	Data source	Timing of data collection
Primary outcome: Provider sealing behavior	*Percentage of eligible lesions receiving a sealant	Electronic health record	B, E
Secondary outcome: Practice cost outcomes	*Total cost, including total program costs, total costs per clinic, and total costs per member per month *Incremental cost effectiveness ratio	Clinic managers and other KPD and PDA staff	B, E
Adoption	*Percentage of introductory sessions, deliberative forums delivered *Percentage of stakeholders attending introductory sessions and deliberative forums *Percentage of post-session surveys completed	Tracking logs, Provider/staff survey	I
Fidelity	*Fidelity of deliberative forums *Percentage of reports delivered to leadership	Tracking logs, Provider/staff survey, transcript coding	I
Acceptability	*Leadership and provider/staff ratings of acceptability of the deliberative loop process	Leadership ratings, Provider/staff survey	I, E
Mechanism: Informed opinions	*Change in top five strategies from the start to the end of the deliberative forum	Output from Common Ground for Action platform	I
Mechanism: Voice	*Difference in Promotive & Prohibitive Voice between UBT meeting and deliberative forum *Perception that leadership will take opinion into consideration *Qualitative analysis of transcripts	Provider/staff survey, transcript coding	I
Implementation strategies selected and adopted	*Percentage of clinics selecting an implementation strategy *Percentage of clinics deploying the selected implementation strategy	Tracking log Provider/staff interview	Q

*Note*. *B* baseline, *I* intervention, *Q* three months after deliberative forum, *E* end of study

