#### Exploratory analysis of putative mediators

We will examine whether having an informed opinion and perceptions of voice mediate the relationship between exposure to the intervention and the use of sealants on NCCL. We will use causal inference methods [28] that have been extended to allow for multiple mediators, as well as exposure-mediator and mediator-mediator interactions. This framework includes both regression-based approaches and approaches based on inverse probability weighting. We will default to the regression-based approach. If model fitting issues are present, we will use the inverse probability weighting approach.

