## Discussion

The purpose of this study is to examine whether introducing the deliberative loop process to an organization enables the clinics within the organization to identify implementation strategies for the organization’s pit-and-fissure dental sealant guideline. The deliberative loop process is a decision-making process that draws on the lived experience of stakeholders and engages difference as a resource. This study will determine whether the deliberative loop process assists clinic leadership at an organization that values and practices shared decision-making in selecting implementation strategies that improve provider adherence to a guideline. There is little information about effective implementation processes for large group dental practices. Our study may be the first to introduce a process that includes both top-down and bottom-up elements. The top-down element supports clinic leadership in their decision-making powers. The bottom-up element elicits the desirability to providers and staff of a range of clinic-level implementation interventions and provides this information to clinic leadership.

Strengths of the study include being guided by theory, having an intervention that addresses identified barriers, and receiving strong support from KPD leadership. With this support, we were able to randomize clinics to steps and optimize the intervention to the needs of the clinics. There are limitations that must be considered, as well. The intervention comprises three components. Because all clinics are receiving all components, should the intervention be successful, we will not have information about the components that contribute to that success. Additionally, because we are conducting this study in the context of one organization with its culture of shared decision-making, should the intervention be successful, we will not be able to determine the cultural parameters that contribute to that success. Finally, the measures characterizing perceptions of voice during the deliberative forum and UBT meetings are both taken following the deliberative forum. Although the retrospective measure of voice during UBT meetings could lack validity and thus bias the results, we believe that the measure could be more valid because the stakeholders have an alternative, the deliberative forum, to use as a comparison. This study will not be able to assess this possibility, however.

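### Voice is always rated for the forum first and for past team meetings second, so any block-order effect, in either direction, cannot be separated from the forum-versus-meeting difference

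*Protocol article*

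**What the plan says.** The Mechanisms subsection of the protocol article defines voice as the opportunity to share one's views and measures it in three ways. The first uses the Promotive and Prohibitive Voice scales, five items each on a 5-point scale. On timing: "Both Promotive Voice and Prohibitive Voice will be assessed immediately following the deliberative forum, via the post-session survey". On order: "Stakeholders will complete the scales first as they characterize the deliberative forum and second as they characterize past UBT meetings". The order is the same for every respondent, and the article mentions no counterbalancing or adjustment for order.

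Table 3 lists as the first measure of the voice mechanism: "Difference in Promotive & Prohibitive Voice between UBT meeting and deliberative forum". The exploratory mediation section then uses voice as a putative mediator: "We will examine whether having an informed opinion and perceptions of voice mediate the relationship between exposure to the intervention and the use of sealants".

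The Discussion acknowledges a neighbouring limitation, that "the measures characterizing perceptions of voice during the deliberative forum and UBT meetings are both taken following the deliberative forum". It adds: "Although the retrospective measure of voice during UBT meetings could lack validity and thus bias the results". It argues that having the forum as a comparison may make the meeting rating more valid, and says the study cannot settle this. Block order is not mentioned.

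**The concern.** Two ratings of the same ten items, made by one person in one sitting, can influence each other. A respondent who has just rated the forum may mark the meetings down by contrast, stay close to the first set of answers, or answer the second set with less care. Because the forum always comes first, every such effect falls on the forum-minus-UBT difference in every respondent.

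At stake is the reading of one of the two proposed mechanisms. A positive difference could not be credited to the forum alone, and a small one could hide a real gain. The order is a feature of the instrument that the article itself fixes, so an analysis plan could not repair it once the data are collected.

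**Working it through.** The article states no expected difference, SD, sample size or test for the voice contrast. The Power section concerns sealants only: "Our null hypothesis is that providers’ rates of placing or treatment planning sealants for occlusal NCCLs will not differ between the non-intervention and intervention periods". There is no figure to reproduce, so the check is one of identifiability, followed by an illustration.

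**1. Fixed order.** Write each rating as a setting mean plus a position effect. Let δ be the forum mean minus the UBT mean, and π the first-position effect minus the second-position effect.

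- Forum first for everyone: E[forum − UBT] = δ + π.
- With columns for intercept, forum and first position, the design has only the rows (1,1,1) and (1,0,0). Its rank is 2 for 3 parameters, so δ and π cannot be separated.

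**2. Randomised order, half and half.**

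- Forum first gives δ + π; UBT first gives δ − π. The average is δ, and half the gap between the two groups is π.
- The rows (1,1,0) and (1,0,1) are added, the rank becomes 3, and both effects can be estimated.
- In a simulation (200 respondents, true difference 0, order effect 0.2 SD of the paired difference) the mean contrast was 0.20 under fixed order and 0.00 under balanced order.

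**3. Where cancellation fails.** Suppose rating the forum first adds c₁ to the later UBT rating, and rating UBT first adds c₂ to the later forum rating. The balanced average is ½[(δ + π − c₁) + (δ − π + c₂)] = δ + (c₂ − c₁)/2, which equals δ only if c₁ = c₂. Comparing first blocks between the two randomised groups gives δ without carry-over from the other block, at the price of a less precise between-respondent comparison.

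**4. Direction.** Contrast, or ratings that drift down later in the survey, widens the difference. Anchoring pulls the UBT rating a fraction a of the way towards the forum rating and leaves (1 − a)δ. That shrinks the difference and cannot create one from zero. Repeating the first answers out of fatigue acts in the same way.

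**5. Illustration of size.** All inputs here are assumptions: a true difference of 0, n independent respondents, a two-sided paired test at 0.05, and an order effect of b SDs of the paired difference. The rejection probability is Φ(b√n − 1.96) + Φ(−b√n − 1.96).

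| n | b = 0.1 | b = 0.2 |
|---|---|---|
| 100 | 17% | 52% |
| 200 | 29% | 81% |
| 400 | 52% | 98% |
| 800 | 81% | about 100% |

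For example, n = 100 and b = 0.1 gives Φ(1 − 1.96) + Φ(−1 − 1.96) = 0.170. The article announces no such test. The table shows only how sensitive the contrast would be if an inflating effect existed.

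**6. Clinics still open to change.** In Table 1 the column of clinics receiving the intervention runs 1, 1, 2, 3, 1, 2, 4, 2 from March to October and sums to 16. Through August it gives 1 + 1 + 2 + 3 + 1 + 2 = 10, leaving 4 + 2 = 6 after the publication date of 28 August 2021. Under the table's note, a forum held late in August may be counted in September, so 6 is better read as a maximum.

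**The case against.** The strongest reply is that this is a choice of survey layout with little riding on it. Several parts of that reply stand.

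- No document gives evidence of an order effect. A reader might infer that a reported gain in voice would be produced partly or wholly by question order. The article does not support this: it gives neither size nor direction, and the percentages above rest on assumed inputs. Nor does it say that the two blocks are adjacent, only which comes first.
- The named effects oppose each other. A reader who assumes that the forum is favoured goes beyond the text.
- Contrast with a forum just attended is already part of the acknowledged limitation and would persist in either block order. Only the increment due to position is new.
- The measure is exploratory. The primary outcome comes from the electronic health record and is not touched. The leadership-responsiveness questions do not depend on this order, and neither does the third voice measure, for which "we will review the transcripts from the deliberative forums using six codes to assess stakeholder voice".
- Randomising order would not remove asymmetric carry-over from the paired difference.

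Two parts do not stand. The Discussion's argument for having the forum as a comparison does not require the forum block to come first, since every respondent has just attended the forum. And the other voice measures do not fill the gap: transcript coding covers forums only, and the responsiveness questions concern what leadership does with feedback. The scale difference is the only direct forum-versus-meeting contrast in voice.

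**Conclusion.** The point holds as a low-priority design improvement. Under the stated order, block position and setting are completely confounded in the forum-UBT voice difference, and the acknowledged retrospective-timing limitation neither states nor resolves this. The size and sign of any resulting bias are unknown.

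The confounding follows from the stated order alone. The claim that randomising removes the effect from the paired difference rests on a further assumption: position effects that are additive and carry-over that is equal in both directions. The effect on the mediation analysis depends on how the two ratings enter it, which the article does not spell out. Nothing here bears on the sealant comparison.

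**What to change.** For every clinic not yet surveyed, randomise per respondent in the existing Qualtrics post-session survey whether the forum or the UBT block comes first, and record the order. Then:

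- include order as a covariate in the analysis of the forum-UBT difference and report the estimated order effect;
- report the first-block-only contrast between respondents as a check on asymmetric carry-over;
- flag clinics already surveyed in the fixed order, analyse them separately or in a sensitivity analysis, and state that their contrast remains confounded with order;
- add block order to the limitations, next to the retrospective timing.

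The cost is a survey setting and one covariate, with no added items, staff or contacts. Coverage is partial: at most about 6 of 16 clinics counted from the publication date. Carrying an order effect estimated in late clinics over to early ones would be a further assumption. Retrospective-recall bias is not removed.

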#### Exploratory measures

To learn more about any effects of the deliberative loop process, project staff will track the percentage of clinics selecting an implementation strategy and deploying their selected implementation strategy. Either the Clinic Manager or a champion identified by the Clinic Manager will track any strategies implemented using a tracking sheet designed for the study and will share the tracking sheet with the study team quarterly. In addition, 3 months after a clinic’s deliberative forum, the Clinic Manager will identify 1–2 clinic staff to participate in a semi-structured interview. The tracking sheets will serve as the basis for the interview, which is designed to obtain additional information about the implementation process. An example of one of the interview questions is as follows: “To your knowledge, was there any follow-up from leadership about possible implementation of strategies to improve sealant placement rates?”

### Data analysis

#### Primary outcome analysis

The non- and intervention sealant rates and their difference will be treated as continuous variables. Using an intention to treat approach, we will use multi-level modeling to compare the sealant rates between the intervention and non-intervention periods. We will use generalized linear models or generalized estimating equations to model the intervention effect while nesting sealant outcomes within provider and provider within clinic and accounting for secular trends, if necessary. In this scenario, our outcome will be whether an eligible E1/E2 lesion was sealed, and we will examine the clinic-level effects of the intervention [22].

The PDA guideline includes children, adolescents, and adults. To enable comparison with studies following the ADA guideline, in addition to analyzing lesions occurring in children, adolescents, and adults, we will also conduct analyses for lesions occurring in just children and adolescents. Per the ADA, we will define “children and adolescents” as persons ranging in age from 6 through 17 years old.

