**Methods:**

Sixteen dental clinics within Kaiser Permanente Northwest Dental will be cluster randomized to determine the timing of receiving the intervention in this stepped-wedge trial. In the three-part deliberative loop intervention, clinic stakeholders engage in the following activities: (1) receive background information, (2) participate in facilitated small-group discussions designed to promote learning from each other’s lived experiences and develop informed opinions about effective clinic-level implementation strategies, and (3) share their informed opinions with clinic leaders, who may then choose to select and deploy implementation strategies based on the stakeholders’ informed opinions. The primary outcome of Reach will be defined as patient-level receipt of guideline-concordant care. Secondary outcomes will include the cost-effectiveness, acceptability, and feasibility of the deliberative loop process. Implementation strategies deployed will be catalogued over time.

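### The primary lesion-level model nests lesions only in provider and clinic; if patients contribute several lesions or clinics drift differently over the year, its standard error is too small

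*Protocol article*

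**What the plan says.** All references are to the protocol article.

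- **Primary outcome analysis.** The section first says that sealant rates will be treated as continuous. It then specifies a model in which the outcome is whether an eligible lesion was sealed, using "generalized linear models or generalized estimating equations to model the intervention effect while nesting sealant outcomes within provider and provider within clinic". Secular trends are to be accounted for only if this proves necessary. No patient level, clinic-by-period term, variance estimator or reference distribution is named.
- **Abstract, Methods.** "The primary outcome of Reach will be defined as patient-level receipt of guideline-concordant care". The patient is therefore the level at which the outcome is described, but is absent from the model hierarchy.
- **Power.** "Scenarios were calculated using intraclass correlations of 0.01, 0.1, and 0.25", using the Hussey and Hughes approach, with 50 or 60 providers per clinic. Each scenario has one ICC and no separate between-period correlation.
- **Study design and recruitment.** There are 16 clinics: 15 randomised in five steps and one vanguard clinic that started earlier. Evaluation runs over 12 calendar months.

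**The concern.** Two sources of correlation are left out of the stated hierarchy.

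1. **Patient.** One patient can have several eligible molar lesions, and these are likely to be decided on together. They share the same clinic and usually the same exposure status, so their correlation bears directly on the precision of the intervention effect.
2. **Clinic by month.** With only a clinic effect, correlation within a clinic is constant over the year. The article itself gives reasons for doubt: clinics have considerable autonomy, each holds monthly improvement meetings, and the evaluation year fell under COVID-19 restrictions.

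In a mixed model for a binary outcome there is no free residual variance to absorb either source. Where they exist, the standard error of the intervention effect is understated and the test rejects too often under no effect. Both omissions push towards a false positive.

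GEE, the other permitted route, has a different weakness. A clinic-clustered sandwich variance tolerates omitted inner levels but is biased downwards with only 16 clusters unless corrected.

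**Working it through.** **Inputs from the article.** Type I error 0.05 (sidedness not stated; two-sided assumed here), "3% rate of placing or treatment planning sealants in the non-intervention period" and "a 10% rate in the intervention period", ICC 0.01, 0.1 and 0.25, 16 clinics, 12 months.

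**Inputs assumed, because the article does not give them.** Lesions per patient, within-patient correlation, lesions per clinic-month, and cluster autocorrelation (CAC, the between-month correlation divided by the within-month correlation).

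**1. The plan's own power figure.** The Hussey-Hughes variance was used with mean rate 0.065, total variance 0.065 × 0.935 = 0.0608 and a difference of 0.07. With 50 or 60 per clinic in each period, power is 99.96% to 100% in every scenario. This agrees with "we will have at least 80% power and close to 100" per cent. If the 50 or 60 were spread over all periods, power would be 57% to 85%, so the statement needs the per-period reading. The calculation sets CAC to 1 and so offers no protection against clinic-specific drift.

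**2. Patient level omitted.** The true variance over the model variance is R = 1 + (m − 1)ρ, for m lesions per patient and correlation ρ left after provider and clinic effects. Type I error = 2[1 − Φ(1.96/√R)].

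| Assumption | R | √R | Type I error |
|---|---|---|---|
| one lesion per patient | 1.0 | 1.00 | 5.0% |
| mostly single lesions | 1.1 | 1.05 | 6.2% |
| m = 2, ρ = 0.5 | 1.5 | 1.22 | 11% |
| m = 3, ρ = 0.7 | 2.4 | 1.55 | 21% |

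**3. Clinic-by-month term omitted.** R = 1 + n × ICC × (1 − CAC)/(1 − ICC), with n lesions per clinic-month. For n = 20:

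| ICC | CAC 1 | CAC 0.8: R | CAC 0.8: type I error |
|---|---|---|---|
| 0.01 | 5.0% | 1 + 20 × 0.01 × 0.2/0.99 = 1.04 | 5.5% |
| 0.1 | 5.0% | 1 + 20 × 0.1 × 0.2/0.9 = 1.44 | 10% |
| 0.25 | 5.0% | 1 + 20 × 0.25 × 0.2/0.75 = 2.33 | 20% |

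A generalised least squares calculation with clinic intercepts and month effects gives the same pattern. For 10 to 100 lesions per clinic-month, type I error at ICC 0.01, 0.1 and 0.25 is:

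- CAC 1: 5.0% throughout.
- CAC 0.9: 5.0–6.1%, 6.2–17.7% and 8.9–34.6%.
- CAC 0.8: 5.0–7.2%, 7.5–27.4% and 12.8–47.9%.

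The exposure pattern was rebuilt from the monthly starts in Table 1 (98 non-intervention and 94 intervention months, 192 in all). The table's period columns add to more than 16 clinics from June to September (for example 8 + 10 in July).

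**4. GEE with 16 clinics.** This was simulated under no effect with a clinic-level sandwich, month effects, a 3% base rate, 48 or 96 lesions per clinic-month and 1,500 runs per scenario. Without correction, type I error is 8.6% to 12.0%, and standard errors are about 10% to 17% too small. With the Mancl-DeRouen correction and t on 14 degrees of freedom it is 2.7% to 5.0%. The excess appears with clinic-by-month variation (10.0–12.0%) and without it (8.6–10.9%), so it comes from the number of clinics and not from the nesting. Monte Carlo error is about 0.6 to 0.8 percentage points.

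**The case against.** The strongest reply is that nothing in the article shows the error rate to be wrong.

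- **The size depends on absent inputs.** Lesions per patient, lesions per clinic-month and CAC are not reported. With single lesions and CAC 1 the stated model holds 5%. This stands, so the finding has to be conditional.
- **The larger ICCs are power scenarios.** They were set for providers per clinic and are not estimates for lesions. At a mean rate of 6.5%, ICC 0.1 and 0.25 imply between-clinic standard deviations of 7.8 and 12.3 percentage points, larger than the mean itself. A clinic SD of 0.5 on the logit scale at a rate of about 6% corresponds to an ICC of about 0.016, where the formula in step 3 (20 lesions, CAC 0.8) gives just under 6%. This stands too: the lower end of the range may be the more realistic.
- **Uncorrected GEE is not stated.** A reader might infer that the plan commits to it. The article names no variance estimator and excludes no correction, and that detail is commonly left to an analysis plan, which is not shown here. The GEE figures therefore support the choice of remedy and are not a fault in the article.
- **The two routes do not share one fault.** The omitted levels affect the mixed model. A clinic-clustered sandwich is robust to them, while the small-cluster bias affects only GEE.
- **Rates as continuous.** An analysis of clinic-month rates would absorb some of this variation. However, the same paragraph goes on to specify the lesion-level model, and the criticism is of that model.

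The hierarchy itself is not answered by these points. It is stated, not left open, and it stops at provider and clinic.

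**Conclusion.** The point holds in conditional form. The article fixes a correlation structure for a binary lesion outcome that omits the patient and assumes constant correlation within a clinic over a year. If either assumption fails, the mixed model's standard error is too small. Under the assumed inputs, type I error runs from about 6% to 21% for an omitted patient level. For an omitted clinic-by-month term with 20 lesions per clinic-month, it runs from 5% (CAC 1) to about 5%, 10% and 20% (CAC 0.8; ICC 0.01, 0.1 and 0.25).

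A reader might conclude that the standard errors are too small as a matter of fact and that the 5% level is not held on either route. The documents do not support that: inflation is nil at CAC 1 with single lesions and slight at ICC 0.01, and the article does not commit to an uncorrected GEE.

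**What to change.** Choose one primary route and state its structure.

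- **Mixed model.** Logistic, with calendar-period fixed effects included from the start and random effects for clinic, clinic by period, provider and patient. Drop the patient term only if it cannot be estimated. Test the intervention effect with clinic-level degrees of freedom.
- **Or GEE.** Cluster at clinic, with a Mancl-DeRouen or Kauermann-Carroll variance and a t reference (14 degrees of freedom in the simulation above). This is robust to the omitted inner levels. The correction is needed because uncorrected GEE with 16 clinics gave about 9% to 12% error in simulation.
- **Permutation test, if used.** Permute only the 15 randomised clinics and hold the vanguard clinic fixed, since it started ahead of the randomised steps.

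The cost is analysis wording, some programming and somewhat wider confidence intervals. At a base rate near 3%, and possibly with many single-lesion patients, the fuller mixed model may need convergence work. If patients mostly contribute one lesion and clinics do not drift, the added variance components should be estimated near zero and little precision is lost.
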